## Abstract

**Background:**

Cervical intraepithelial neoplasia (CIN) is the premalignant condition of cervical cancer. Whereas not all high grade CIN lesions progress to cervical cancer, the natural history and risk of progression of individual lesions remain unpredictable. Therefore, high-grade CIN is currently treated by surgical excision: large loop excision of the transformation zone (LLETZ). This procedure has potential complications, such as acute haemorrhage, prolonged bleeding, infection and preterm birth in subsequent pregnancies. These complications could be prevented by development of a non-invasive treatment modality, such as topical imiquimod treatment.

The primary study objective is to investigate the efficacy of topical imiquimod 5 % cream for the treatment of high-grade CIN and to develop a biomarker profile to predict clinical response to imiquimod treatment. Secondary study objectives are to assess treatment side-effects, disease recurrence and quality of life during and after different treatment modalities.

**Methods/design:**

The study design is a randomized controlled trial. One hundred forty women with a histological diagnosis of high-grade CIN (CIN 2–3) will be randomized into two arms: imiquimod treatment during 16 weeks (experimental arm) or immediate LLETZ (standard care arm). Treatment efficacy will be evaluated by colposcopy with diagnostic biopsies at 20 weeks for the experimental arm. Successful imiquimod treatment is defined as regression to CIN 1 or less, successful LLETZ treatment is defined as PAP 1 after 6 months. Disease recurrence will be evaluated by cytology at 6, 12 and 24 months after treatment. Side-effects will be evaluated using a standardized report form. Quality of life will be evaluated using validated questionnaires at baseline, 20 weeks and 1 year after treatment. Biomarkers, reflecting both host and viral factors in the pathophysiology of CIN, will be tested at baseline with the aim of developing a predictive biomarker profile for the clinical response to imiquimod treatment.

**Discussion:**

Treatment of high-grade CIN lesions with imiquimod in a selected patient population may diminish complications as a result of surgical intervention. More knowledge on treatment efficacy, side effects and long-term recurrence rates after treatment is necessary.

**Trial registration:**

EU Clinical Trials Register EU-CTR2013-001260-34. Registered 18 March 2013.

Medical Ethical Committee approval number: NL44336.068.13 (Medical Ethical Committee Maastricht University Hospital, University of Maastricht).

Affiliation: Maastricht University Hospital.

Registration number ClinicalTrials.gov: NCT02329171.

## Background

Cervical intraepithelial neoplasia (CIN) is the premalignant condition of cervical cancer and is caused by cervical human papillomavirus (HPV) infection [1]. The natural history of individual CIN lesions is unpredictable. Approximately 30 % of high-grade CIN progresses to cervical cancer [2, 3]. On the contrary, recent evidence suggests that spontaneous regression occurs in approximately 20–40 % of high-grade lesions [4–7]. Current histopathological assessment is unable to differentiate between lesions that will progress to cervical cancer and those that will regress spontaneously. Therefore, all high-grade CIN lesions are currently treated by surgical excision, consisting of large loop excision of the transformation zone (LLETZ). This treatment is associated with potential complications. Short term complications include pain, vaginal discharge and bleeding. The most serious late complication is premature birth in subsequent pregnancy, probably due to cervical insufficiency [8–10]. Evidence shows a two fold increase in premature birth between 32/34 and 37 weeks in patients who were treated with LLETZ. Furthermore, cervical surgery for CIN may be associated with subfertility. A recent case–control study in 152 patients who underwent cervical surgery showed a twofold increase in prolonged time to conception (16.4 % vs 8.6 %) for patients who underwent LLETZ [11]. Since cervical dysplasia is most common in women of childbearing age, these potential complications are of special interest to the patient population and surgical intervention should be avoided if possible. Therefore, an effective non-invasive treatment modality is needed. A potential agent in non-invasive therapy is imiquimod cream. Imiquimod is an immunomodulator with antiviral and anti-tumour effects. It is a toll-like receptor 7 agonist and induces up regulation of interferon and activation of dendritic cells [12]. It is currently used in treatment of basal cell carcinoma, actinic keratosis and external genital warts in adults. As an off-label drug, it has also been proven effective in the treatment of HPV related vulvar intraepithelial neoplasia (VIN) [13]. The use of imiquimod in CIN has been studied by several authors [7, 14, 15]. Only one randomized controlled trial was conducted, evaluating the efficacy of imiquimod treatment in high-grade CIN [7]. Grimm et al. included 59 patients, who were randomized for treatment with imiquimod or placebo during 16 weeks. The study results are promising: both histologic regression and complete remission of high-grade CIN was significantly more frequent in patients treated with imiquimod, compared to the control arm (73 % vs 39 % and 47 % vs 14 % respectively). However, side-effects seem common and long-term outcomes are unknown.

Ideally, the response to imiquimod treatment of an individual patient would be predictable. Previous studies have shown that the natural behaviour of CIN lesions can be partially predicted by biomarker models, consisting of markers that reflect host, viral and cellular factors [4, 16]. This study aims to develop a similar biomarker prediction model for the individual response to imiquimod treatment, in order to enable individualized treatment of CIN lesions.

This study aims to confirm the short and long term efficacy of imiquimod 5 % cream in the treatment of high-grade CIN, as well as to evaluate clinical applicability by assessment of side-effects and quality of life during and after treatment. Additionally, it aims to develop a biomarker prediction model for clinical response to imiquimod treatment of high-grade CIN. For this purpose, we designed a randomized controlled trial with two arms, in which imiquimod treatment is compared to standard treatment by LLETZ. The trial was designed according to the CONSORT guidelines.

## Methods

### Setting and study population

The study will be started at the outpatient clinic of gynecologic oncology, Maastricht University Medical Center, the Netherlands and is intended as a multi-center trial in the future. Inclusion criteria are newly diagnosed, histologically confirmed high-grade CIN lesions (CIN 2–3) and age above 18 years. Exclusion criteria are previous histologically confirmed high-grade CIN (CIN 2–3), concomitant vulvar and/or vaginal intraepithelial neoplasia, previous cervical malignancy, current malignant disease, immunodeficiency (including HIV/AIDS and immunodepressive medication), pregnancy or lactation and legal incapability.

### Study objectives and outcome measures

The primary study objectives and outcome measures are:Assessment of treatment efficacy of imiquimod treatment for high-grade CIN, as compared to LLETZ treatment. Successful treatment for the experimental (imiquimod) arm is defined as regression to CIN 1 or less in diagnostic biopsies at 20 weeks follow-up. Successful treatment for the LLETZ arm is defined as normal cytology at 6 months follow-up. Based upon earlier studies, we hypothesize that 50–75 % of patients in the experimental (imiquimod) arm will show regression to CIN 1 or less.These two different outcome measures (cytology in the LLETZ arm and histology in the experimental arm) were selected in order to optimize the assessment of treatment efficacy, whilst limiting overtreatment of patients (performing unnecessary biopsies or LLETZ treatments). For the experimental arm, it is assessed by colposcopy with diagnostic biopsies and for the LLETZ arm it is assessed by cytology. Regarding efficacy of LLETZ treatment, the significance of resection margins of the LLETZ specimen is controversial and is not advised in guidelines as outcome measure of LLETZ efficacy. Therefore, regular follow-up cytology at six months was selected as outcome measure, as is also done in clinical practice. Regarding imiquimod treatment, histological assessment of treatment efficacy was selected as outcome measure, in order to optimize the assessment of potential residual disease. Biopsies were chosen rather than a standard LLETZ procedure to evaluate residual disease, to prevent overtreatment.Development of a biomarker model to predict adequate response to imiquimod treatment.

Secondary study objectives and outcome measures are:To determine the incidence and severity of side effects of LLETZ and imiquimod therapy, scored by the Common Terminology Criteria for Adverse Events guidelines.To estimate disease recurrence rates for both arms at 6, 12 and 24 months follow-up, defined as abnormal cervical cytology. The follow-up term starts after treatment is finished.To assess Quality of life (QoL) for both arms before, during and after treatment (at 0 and 20 weeks and after 1 year) by the following QoL questionnaires: [1] Medical Outcomes Study 36-Item Short-Form General Health Survey (RAND 36), to assess generic health-related quality of life, [2] the European Organization for Research and Treatment of Cancer (EORTC) QLQ-C30, to assess cancer-specific health-related quality of life, and [3] the European Organization for Research and Treatment of Cancer (EORTC) QLQ-CX24, to assess cervical cancer specific quality of life, including sexual functioning.

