Patients in the experimental arm are treated with imiquimod 5 % cream during 16 weeks. Imiquimod 5 % cream is administered in a vaginal applicator, containing 12,5 mg of imiquimod (one sachet). The cream is administered three times per week. The cream is administered by patients themselves at night, before going to bed. A vaginal shower is performed in the morning in order to remove cream remainders. In case of mild systemic drug-related side effects, patients are offered a prescription for anti-inflammatory drugs (paracetamol or NSAID). In case of more severe or persistent systemic or severe local side effects (Common Terminology Criteria for Adverse Events grade 2 or higher), the frequency of imiquimod application is decreased to twice per week, and subsequently to once per week if side effects persist. Imiquimod treatment is discontinued if side effects are unacceptable to patients hereafter. Subjects should use adequate contraception in order to prevent pregnancy. Subjects should not have vaginal sexual intercourse from the time of application of the imiquimod cream until the vaginal shower the next morning. A control colposcopy with diagnostic biopsies is performed after 10 weeks to rule out disease progression. Biopsies are performed at the initial high-grade CIN lesion site and at any other suspect site, with a minimum of two. In case of progressive disease (defined as increase in lesions size with stable disease grade, higher disease grade or invasive disease), surgical excision is performed.

Treatment efficacy for the experimental arm is evaluated at 20 weeks follow-up, by colposcopy with diagnostic biopsies. Biopsies are performed by using a cervical biopsy specimen forceps (Aesculap ER055R), at the initial high-grade CIN lesion site and at any other suspect site, with a minimum of two. In case of persistent or progressive disease (> CIN 1), surgical excision is performed.

Patients in the standard treatment arm undergo LLETZ at short term (within 4 weeks after the diagnosis). Excision of the transformation zone and macroscopic lesions is performed by a monopolar loop electrode, under local anaesthesia. A summary of study interventions can be found in Fig. 1.

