### Statistical methods

Logistic regression analysis will be used to evaluate treatment efficacy of imiquimod treatment, compared to LLETZ treatment. Covariates in this analysis are age at diagnosis, CIN grade, smoking and HPV-subtype. Analysis will be based on intention-to-treat protocol. A biomarker prediction model for adequate response to imiquimod treatment will be developed by backward logistic regression analysis of biomarkers based on likelihood ration tests. The prevalence and severity of side effects of imiquimod and LLETZ treatment will be presented as proportions and means with 95 % confidence intervals. Differences in the rates of overall side-effects and severe side-effects between the imiquimod and LLETZ arms will be tested with a chi-square test. Disease recurrence rates after 6, 12 and 24 months will be evaluated in successfully treated patients by use of multiple logistic regression analysis, after adjustment for age at diagnosis, CIN grade, smoking, sexual behaviour and HPV subtype. Repeated-measures analysis of variance will be used to test for between-group differences over time in Quality of Life scores. Analysis of covariance will be used to compare group scores on these outcomes at 20 weeks and at 12 months, with adjustment for baseline scores.

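### The imiquimod recurrence rate mixes true recurrence with persistence of CIN 1 that the trial has already counted as treatment success

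*Protocol article*

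**What the plan says.** Five statements in the protocol article bear on this.

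- Study objectives and outcome measures, first primary objective: "Successful treatment for the experimental (imiquimod) arm is defined as regression to CIN 1 or less in diagnostic biopsies at 20 weeks follow-up". Residual CIN 1 is a success.
- Interventions, on the week-20 colposcopy: "In case of persistent or progressive disease (> CIN 1), surgical excision is performed". Residual CIN 1 is therefore left in place.
- Study objectives and outcome measures, secondary objectives: "To estimate disease recurrence rates for both arms at 6, 12 and 24 months follow-up, defined as abnormal cervical cytology". No grade cut-off is given, and no earlier normal result is required.
- Statistical methods: recurrence "will be evaluated in successfully treated patients by use of multiple logistic regression analysis". Women with CIN 1 at week 20 belong to this set.
- For the other arm, the objectives section says "Successful treatment for the LLETZ arm is defined as normal cytology at 6 months follow-up", and the Abstract gives the class: "successful LLETZ treatment is defined as PAP 1 after 6 months". By inference, any result above PAP 1 is abnormal.

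The Background states the purpose these data serve: "This study aims to confirm the short and long term efficacy of imiquimod", with high-grade CIN as the disease treated.

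**The concern.** Recurrence ordinarily means disease that cleared and came back. Here the two definitions use different thresholds. The disease at entry is CIN 2-3 and the success threshold is CIN 1, yet the recurrence threshold is any cytological abnormality. The Interventions section does not treat CIN 1 at week 20 as persistent disease, but the same untouched lesion can appear as recurrent disease a few months later.

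The long-term efficacy result is at stake. A reader of the final report would take the imiquimod recurrence rate as the frequency with which successfully treated disease returns. Part of it may be low-grade disease that never left and that the trial had accepted. The starting state also differs between arms: LLETZ successes begin from normal cytology, while imiquimod successes may begin with a known lesion. The distortion therefore works against imiquimod in the comparison.

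**Working it through.** The protocol gives no expected recurrence rate, so there is no stated figure to reproduce. Its 42 per arm concerns the primary outcome and does not enter here. The roughly 70 per arm for secondary outcomes is given without inputs.

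**Step 1: following one woman through the text.** Week-20 biopsy shows CIN 1, so she is a success. No excision follows. She enters the recurrence analysis set. If the lesion persists and her smear at 6, 12 or 24 months is abnormal, she is a recurrence. No section redirects her. The planned model adjusts for CIN grade, but that covariate is not described as the week-20 grade, and LLETZ women have no week-20 biopsy.

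**Step 2: how many successes could be affected.** The Background says of the cited placebo-controlled trial that "both histologic regression and complete remission of high-grade CIN was significantly more frequent in patients treated with imiquimod", and gives 73% regression and 47% complete remission on imiquimod. *Assumption A:* the whole gap is residual CIN 1.

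- Share of successes with residual CIN 1 = (0.73 − 0.47)/0.73 = 0.26/0.73 = 0.356, or 36%.
- With 70 women evaluated: 70 × 0.73 = 51.1 successes, of whom 70 × 0.26 = 18.2 have residual CIN 1.
- With 20% withdrawal (56 women): 40.9 successes, 14.6 with residual CIN 1. The share is the same.
- The other 47/73 = 64% can contribute only true recurrence.

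**Step 3: how many would be labelled recurrent through persistence alone.** Share labelled = 0.356 × P(abnormal smear due to persisting CIN 1). The documents give no value for this probability. *Assumption B:* 20-80%.

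- 0.356 × 0.20 = 0.07
- 0.356 × 0.50 = 0.18
- 0.356 × 0.80 = 0.28

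The probability can be split into persistence × abnormal smear given persistence (both assumed):

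- 25% × 50%: 0.356 × 0.125 = 4.5%
- 50% × 70%: 0.356 × 0.35 = 12.5%
- 75% × 70%: 0.356 × 0.525 = 18.7%
- 100% × 100%: 36%, the ceiling under Assumption A

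**Step 4: timing.** Interventions anchors follow-up visits to the start of treatment, whereas the recurrence objective starts the follow-up term after treatment ends. The 6-month (26-week) smear is then 26 − 20 = 6 weeks after the week-20 biopsy, or (16 + 26) − 20 = 22 weeks after it. Persistence could differ between these two times, so a single probability for the 6-month visit is fragile.

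**The case against.** Several counter-arguments have force.

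- **The outcome is not simply persistence.** A reader might infer that it measures persistence instead of recurrence. The documents do not support that: women with no CIN at week 20 who later turn abnormal are correctly counted, and under Assumption A they are the larger group. Nor is every persisting CIN 1 counted, because the test changes from biopsy to cytology and only an abnormal smear counts.
- **The figures are mostly assumption.** This stands. The Background defines neither regression nor complete remission. Regression there could include a fall from CIN 3 to CIN 2, so the 26-point gap need not be residual CIN 1. The 36% and 7-28% are illustrations.
- **High-grade results are recoverable.** This also stands. Cytology is read on the Papanicolaou system by two analysts and collected at 6, 12 and 24 months. The defect lies in how the outcome is defined and named; the information is not lost.
- **Any abnormal smear is ordinary follow-up, and the outcome is secondary.** That justifies collecting and reporting it, and it limits the weight of the point. It does not justify calling the result recurrence when the success threshold is CIN 1.

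None of these separates accepted CIN 1 that persists from disease that returns.

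**Conclusion.** The success and recurrence definitions do not fit together within the imiquimod arm. Whenever accepted CIN 1 persists and yields an abnormal smear, it is counted as recurrence, which biases that arm's rate upward. The direction follows from the text; the size does not. Under Assumption A at most 36% of imiquimod successes could be affected, and under Assumption B as well, about 7-28%. The problem is absent among women with no CIN at week 20. It should be settled before analysis because it changes what the long-term result can be said to show, but it concerns a secondary outcome and leaves the primary comparison untouched.

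**What to change.** In the secondary objectives and in Statistical methods:

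1. Define recurrence of high-grade disease, in both arms, by one prespecified high-grade Papanicolaou cut-off.
2. Keep any abnormal cytology as a separately named outcome.
3. Report imiquimod successes separately for no CIN and for CIN 1 at week 20. In the CIN 1 group, label abnormal cytology below the cut-off as possible persistence, not recurrence. This split is descriptive, since LLETZ women have no week-20 histology.

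The Papanicolaou results and the week-20 grade are already recorded, so the change needs only wording and one extra table. The definition should not rely on follow-up histology: Data collection lists none after week 20, and biopsies taken only after abnormal smears would be selectively available. No visit, treatment or clinical rule changes.

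The cost is fewer events at the high-grade cut-off, hence wider intervals. The change also leaves one separate problem in place. LLETZ success itself requires normal cytology at 6 months, so if the same smear serves both purposes, 6-month recurrence among LLETZ successes is zero by definition under either cut-off.

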### Interventions

After informed consent is obtained, patients are equally randomized into one of two arms:*Experimental arm*. Patients in this arm are treated by a 16-week regime of imiquimod 5 % cream.*Standard arm*. Patients in this arm receive standard treatment by LLETZ.

Follow-up visits are anchored to the start of the treatment (either imiquimod or LLETZ). Cytological assessment will be performed by two independent trained cytology analysts, according to the Papanicolaou system. In case of inconsistent results, a consensus will be reached by discussion. The histopathological assessment of cervical biopsies will be performed by two independent pathologists according to national guidelines, based on the WHO guidelines. In case of inconsistent results, a consensus will be reached by discussion. CIN diagnosis will be based on evaluation of histological features concerned with differentiation, maturation and stratification of cells and nuclear abnormalities, in combination with p16 staining. In CIN 1 there is good maturation with minimal nuclear abnormalities and few mitotic figures. Undifferentiated cells are confined to the deeper layers (lower third) of the epithelium. Mitotic figures are present, but not very numerous. Cytopathic changes due to HPV infection may be observed in the full thickness of the epithelium. CIN 2 is characterized by dysplastic cellular changes mostly restricted to the lower half or the lower two-thirds of the epithelium, with more marked nuclear abnormalities than in CIN 1. Mitotic figures may be seen throughout the lower half of the epithelium. In CIN 3, differentiation and stratification may be totally absent or present only in the superficial quarter of the epithelium with numerous mitotic figures. Nuclear abnormalities extend throughout the thickness of the epithelium. Many mitotic figures have abnormal forms.

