**Fig. 1 Fig1:**
[figure not shown]
Summary of study interventions

The imiquimod treatment period was set at 20 weeks, in order to realize adequate treatment efficacy of imiquimod, while minimizing the risk of progression of cervical dysplasia to invasive disease. Progression of CIN into cervical cancer is considered to be a slow process. The annual risk of progression of CIN 3 to invasive cervical cancer is estimated to be less than 1 % [17]. We identified ten studies in which patients with high-grade CIN underwent watchful waiting for a set period of time [4, 6, 7, 18–24]. A total of 637 patients were included either as a control group, receiving no treatment during 6 weeks to 15 months, or followed during the period between diagnosis and LLETZ. Three cases of invasive disease were identified: all occurred in the same study after 16 weeks of observation. The possibility of invasive disease already present at the initial colposcopy (due to biopsy error) cannot be excluded. Based on these results, we set the maximum treatment period at 20 weeks and we included an additional control colposcopy with diagnostic biopsies after 10 weeks. When no disease progression is detected during this colposcopy, the imiquimod treatment can be continued until the 20 weeks colposcopy.

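### Quality of life during treatment is a stated objective, but under the 16-week imiquimod course no questionnaire falls on treatment in either arm

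*Protocol article*

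**What the plan says.** Study objectives and outcome measures sets the secondary objective "To assess Quality of life (QoL) for both arms before, during and after treatment (at 0 and 20 weeks and after 1 year"). The Background gives the same aim: "to evaluate clinical applicability by assessment of side-effects and quality of life during and after treatment". The Discussion repeats it when it defines clinical applicability.

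The schedule is consistent wherever it appears. The Abstract says "Quality of life will be evaluated using validated questionnaires at baseline, 20 weeks and 1 year after treatment". Data collection lists quality of life at baseline, at the 20-week visit and at 12 months. It lists none at the 6-, 10- and 14-week contacts.

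The treatment period is stated in two ways. Interventions says "Patients in this arm are treated by a 16-week regime of imiquimod" and later "Patients in the experimental arm are treated with imiquimod 5 % cream during 16 weeks"; the Abstract also gives 16 weeks. The text below Fig. 1 says "The imiquimod treatment period was set at 20 weeks, in order to realize adequate treatment efficacy of imiquimod" and allows imiquimod to run on to the 20-week colposcopy. Interventions counts follow-up visits from the start of either treatment.

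For analysis, Statistical methods says "Repeated-measures analysis of variance will be used to test for between-group differences over time in Quality of Life scores". It adds analyses of covariance at 20 weeks and at 12 months, adjusted for the baseline score.

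**The concern.** An objective that names three phases (before, during, after) needs a measurement in each. Here the middle phase appears to have none. The phase matters because the case for imiquimod rests on sparing women the burden of surgery. The Background says that imiquimod side effects seem common, and it lists pain, discharge and bleeding as short-term complications of LLETZ. If the first score after baseline comes when either burden may have passed, similar scores in the two arms cannot be read as similar quality of life during treatment. A score not collected on treatment cannot be recovered by later analysis.

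A smaller question concerns the over-time test. Repeated-measures ANOVA in its classical form uses only women with all three questionnaires, and the plan expects some withdrawal and does not replace women who withdraw.

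**Working it through.** **1. Timing**

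Inputs: imiquimod for 16 weeks (Abstract, Interventions) or 20 weeks (text below Fig. 1); visits counted from treatment start (Interventions); LLETZ a single procedure (Interventions); questionnaires at 0 weeks, 20 weeks and 1 year (Abstract, Study objectives, Data collection).

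Gap = questionnaire week − last treatment week.

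| Reading | Imiquimod arm, week 20 | LLETZ arm, week 20 | Questionnaires between start and end of imiquimod |
|---|---|---|---|
| 16-week text | 20 − 16 = 4 weeks after the planned last application | 20 weeks after the procedure | 0 of 3 |
| 20-week text | 20 − 20 = 0, the end of treatment | 20 weeks after the procedure | 1 of 3, at the very end |

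Week 0 is the baseline and 1 year is after treatment on either reading. The Abstract's wording could also be read as counting 20 weeks from the end of treatment. That would move the questionnaire later still and would not help.

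**2. Contacts already in the schedule (Data collection)**

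| Contact | Imiquimod arm | LLETZ arm | Quality of life |
|---|---|---|---|
| 6 weeks | adverse effects | adverse effects, by report form | no |
| 10 weeks | adverse effects, compliance, histology | nothing listed | no |
| 14 weeks | adverse effects | nothing listed | no |

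Week 6 is the only contact before week 20 that collects data in both arms. It is on treatment for imiquimod under either duration, and early after the procedure for LLETZ.

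**3. The over-time test**

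The plan gives a withdrawal rate of about 20% in the primary sample size. It reproduces: 42 / (1 − 0.20) = 52.5, rounded up to the stated 53. The figure of roughly 70 per arm for secondary outcomes has no stated inputs and cannot be reproduced.

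*Assumption:* the same 20% applies to questionnaires. A complete-case ANOVA then uses 70 × 0.80 = 56 per arm.

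Detectable difference in SD units (two-sided 5%, 80% power, two means, no gain from covariates) = (1.960 + 0.842) × √(2/n):

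- n = 70: 2.802 × 0.169 = 0.47 SD
- n = 56: 2.802 × 0.189 = 0.53 SD

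*Range, assuming independent missingness m at each of the two later visits:* n = 70 × (1 − m)².

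- m = 5%: 63 per arm, 0.50 SD
- m = 10%: 57 per arm, 0.53 SD
- m = 20%: 45 per arm, 0.59 SD

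The planned ANCOVAs each need only the baseline and one later score. A woman seen at 20 weeks and lost afterwards stays in the 20-week comparison.

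**The case against.** The best defence of the schedule is the text below Fig. 1. If treatment runs to 20 weeks, the week-20 questionnaire coincides with the end of imiquimod. That is a fair reason to make the finding conditional on the 16-week text. It does not remove it: the earlier on-treatment contacts would still carry no questionnaire, and the LLETZ arm would still have none near its procedure.

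A second defence is that treatment burden is captured elsewhere. Side effects have their own objective and are recorded at 6, 10, 14 and 20 weeks for imiquimod. This limits the damage, but the plan treats quality of life during treatment as a separate aim.

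On the analysis, the defence is stronger. The article does not say that women with a missing questionnaire are excluded, and missing-data handling may be in documents not shown. The ANCOVAs already keep women who miss the other visit. They do not replace the over-time test, so naming a better model for that test remains useful but secondary.

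A reader might go further and infer three things that the documents do not support:

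- *The trial will find no difference because both arms have recovered by week 20.* No recovery times are given. At week 20 imiquimod women have biopsies, and those with more than CIN 1 go on to excision, about 27% (100 − 73) at the planning regression rate. The arms need not look alike.
- *Missing questionnaires make imiquimod look better tolerated.* The plan treats stopping the cream and leaving the study separately. Nothing says that women who stop the cream stop answering.
- *The plan throws away the 20-week scores of women lost later.* The ANCOVA at 20 weeks uses them.

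**Conclusion.** The mismatch holds. Under the 16-week text, none of the three questionnaires is on treatment in either arm, and week 20 falls 4 weeks after the planned last application. A null quality-of-life result may therefore miss treatment burden. Under the 20-week text the gap narrows to one score at the very end of imiquimod, and the LLETZ arm is unchanged. The two durations must be reconciled; which of them is right is not a matter for this review.

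This is a gap in a secondary objective and does not touch the primary comparison, but it is cheap to close and deserves to be closed. The point about repeated-measures ANOVA is an improvement rather than an error. Its size, about 56 of 70 women per arm and a detectable difference of 0.53 rather than 0.47 SD, rests on borrowing the withdrawal rate from the primary sample size. The direction of any bias is not shown.

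**What to change.** 1. Give the same three quality-of-life questionnaires at the existing 6-week contact in both arms, and describe that time as on treatment for imiquimod and early after the procedure for LLETZ. Cost: one extra questionnaire set per woman at a contact that already takes place. Women already past week 6 will lack this score, and the report should say so.
2. If this is not done, remove *during* from the objective in Study objectives and outcome measures, and from the matching statements in the Background and Discussion. Cost: wording only.
3. Reconcile the 16-week and 20-week statements of the treatment period, so that the place of the week-20 questionnaire relative to treatment is fixed.
4. For the over-time test, replace repeated-measures ANOVA with a linear mixed model on all available post-baseline scores, with baseline score, arm, visit and arm-by-visit as terms. The 20-week and 12-month contrasts can come from the same model. Cost: none beyond the change of text.
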